## Abstract

**Background:**

Development of obesity and obesity-related diseases, such as type 2 diabetes mellitus and nonalcoholic fatty liver disease (NAFLD), is associated with altered gut microbiota composition. The aim of this study is to investigate associations among dietary compounds, intestinal cell function, and gut microbiota composition. We hypothesize that dietary lipid intake is associated with Paneth cell and goblet cell properties that affect gut microbiota composition.

**Objective:**

The primary objective of this study is to determine whether a difference in dietary intake is associated with a difference in intestinal mucin-2 expression and gut microbiota composition.

**Methods:**

This is a single-center prospective study, including 1 obese group undergoing laparoscopic Roux-en-y gastric bypass and 2 lean control groups undergoing either laparoscopic cholecystectomy or upper gastrointestinal endoscopy (n=228). During laparoscopy, biopsies will be taken of visceral fat (omentum majus), liver, muscle tissue of the abdominal wall, and subcutaneous fat. In the obese group, a small segment of the jejunum will be collected for analysis, which will be compared with an endoscopically derived jejunal biopsy from the upper gastrointestinal endoscopy control group. Stool samples for microbiota profiling will be collected at baseline and 1 year after surgery. Primary outcomes are fecal microbiota composition and mucus characteristics. Secondary outcomes include Paneth cell phenotype, body weight, diet composition, glucose tolerance, resolution of comorbidities, and weight loss 1 year after surgery.

**Results:**

This trial is currently open for recruitment. The anticipated completion date is December 2019.

**Conclusions:**

The Diet-Induced Alteration of Microbiota and Development of Obesity, NAFLD, and Diabetes study will improve insight into the pathophysiology of obesity and its associated metabolic disorders. Better understanding of weight loss failure and weight regain following bariatric surgery might also behold new therapeutic opportunities for obesity and obesity-related comorbidities.

**Trial Registration:**

Netherlands Trial Register NTR5660; https://www.trialregister.nl/trial/5540 (Archived by WebCite at http://www.webcitation.org/78l7jOZre)

**International Registered Report Identifier (IRRID):**

DERR1-10.2196/11553

## Introduction

Obesity-associated diseases, such as type 2 diabetes mellitus (T2DM) and nonalcoholic fatty liver disease (NAFLD), are major public health issues worldwide, affecting more than 6% and 25% of the world population, respectively [1,2]. The influence of gut bacteria on the development of obesity and metabolic syndrome is not entirely understood.

Numerous experimental studies show that gut bacteria are influential in the development of obesity. For example, transplantation of gut microbiota from obese into germ-free mice has been shown to cause a higher fat mass increase than transplantation of lean microbiota. [3] Thus, altering gut bacterial composition can have a direct effect on body weight. In addition, gut microbiota might play a potential role in the treatment of T2DM. Indeed, targeting gut microbiota by antibiotic treatment has been shown to improve body weight and glucose tolerance of high-fat fed mice [4,5]. Prebiotic, as well as probiotic, treatment also improves glucose metabolism in high-fat diet-induced diabetes [6,7]. Moreover, infusion of gut microbiota from lean human donors into subjects with metabolic syndrome has been reported to result in increased insulin sensitivity [8], demonstrating the feasibility of gut microbiota modulation for improving glucose homeostasis in a clinical setting. NAFLD is the hepatic manifestation of the metabolic syndrome, characterized by ectopic fat accumulation in the liver. Previous animal studies have indicated a link between development of NAFLD and gut microbiota. For example, gut microbiota transplantation from mice with NAFLD to wild-type recipients led to replication of the NAFLD phenotype, showing that NAFLD is transmissible through gut bacteria [9]. The factors that underlie the microbiota alterations in obesity, T2DM, and NAFLD are unclear, although the genetic makeup of the host is considered to play a significant role. Gut microbiota composition and function are strongly affected by endogenous antimicrobial proteins secreted by Paneth cells in the small intestine [10], as well as by mucus components made by intestinal goblet cells [11]. Next to these host factors, dietary macronutrient composition has a strong impact on gut microbiota [12]. In particular, high-fat diets decrease abundance of *Akkermansia muciniphila*, a mucus associated bacterium that has been found to be inversely correlated with body mass in mice [13]. Besides this specific bacterium, diet also has an effect on the ratio of 2 major intestinal bacterial phyla: high-fat diets induce Firmicutes while reducing Bacteroidetes [3,14,15].

The data on changes in gut microbiota composition after bariatric surgery are relatively limited. Within 3 months after Roux-en-Y gastric bypass (RYGB), gut microbiota has been found to be more diverse with an increased relative abundance of *Akkermansia muciniphila* [16]. However, most of the available clinical studies have small sample sizes and only analyze fecal samples collected at 12 months postoperatively or less. The possible impact of gut microbiota on failure to maintain weight loss after bariatric surgery is still unknown. This phenomenon, better known as secondary nonresponse, can occur in up to 25% of all patients who undergo RYGB surgery, and it can become apparent at 12 to 24 months postoperatively [17,18]. A recent study showed no difference in microbiota composition between a group of patients following RYGB surgery who obtained more than 50% excess weight loss after 2 years and a group of patients who did not reach that weight goal [19]. Unfortunately, that study lacked baseline samples, and that study had a very small sample size. The overall aim of the proposed study is to investigate associations among intake of dietary compounds, intestinal cell function, and gut microbiota composition. The primary objective is to determine the relationship between diet and intestinal mucin-2 expression in obesity. Secondary objectives are assessment of the relationships among diet, intestinal goblet cell and Paneth cell function, and gut microbiota composition, as well as changes in these parameters in association with secondary nonresponse, presence of T2DM, and NAFLD. We hypothesize that dietary lipid intake is associated with Paneth cell and goblet cell properties that affect gut microbiota composition.

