### Statistical Analysis

#### Power

Sample size is calculated on the basis of the smallest expected difference in the main outcome parameter, that is, intestinal mucin-2 expression, using G*power 3 (Erdfelder, Faul, and Buchner, 1996). A pilot study with lean nondiabetic and obese diabetic rats revealed a difference in expression of 1.00±0.71 versus 0.65±0.78. Taking this into account and using a significance level of 0.05 and a power of 80%, each group will require 73 patients. Considering an expected loss to follow-up of 5%, 76 patients need to be included in each group, amounting to 228 patients in total.

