#### Analysis of Primary and Secondary Outcome Parameters

SPSS will be used for statistical analysis (IBM Corp, Released 2013, IBM SPSS Statistics for Macintosh, Version 22.0.). A 2-tailed *P* value <.05 will be considered statistically significant. To allow comparisons among groups, data will be tested for normal distribution, and appropriate statistical tests will be applied, potentially including Students *t* test, Mann-Whitney U test, analysis of variance, Kruskal-Wallis test, Chi-square test, or Fisher exact test.

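### The 80% power belongs to a lean-versus-obese difference in mucin-2, not to the diet–mucin-2 association that is the primary objective

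*Protocol article*

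**What the plan says.** The Introduction of the protocol article puts the primary question as follows: "The primary objective is to determine the relationship between diet and intestinal mucin-2 expression in obesity". The Objective paragraph of the abstract asks "whether a difference in dietary intake is associated with a difference in intestinal mucin-2 expression and gut microbiota composition". The hypothesis narrows the exposure to fat: "We hypothesize that dietary lipid intake is associated with Paneth cell and goblet cell properties that affect gut microbiota composition". Under Dietary Habits, every participant keeps a 7-day food record at baseline.

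The Power section takes a different contrast. "Sample size is calculated on the basis of the smallest expected difference in the main outcome parameter, that is, intestinal mucin-2 expression". Its input is "A pilot study with lean nondiabetic and obese diabetic rats revealed a difference in expression of 1.00±0.71 versus 0.65±0.78", and its result is "using a significance level of 0.05 and a power of 80%, each group will require 73 patients". An allowance of 5% for loss brings this to 76 per group and 228 in total.

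The section on analysis of primary and secondary outcomes says: "To allow comparisons among groups, data will be tested for normal distribution, and appropriate statistical tests will be applied". It then offers, as possibilities, the t test, Mann-Whitney, analysis of variance, Kruskal-Wallis, chi-square and Fisher tests. Study Population defines three groups: obese, lean cholecystectomy and lean endoscopy. Study Design frames the cross-sectional part as obese against lean. Under Biopsies, jejunal tissue comes only from the obese and endoscopy groups, so mucin-2 is available in two of the three.

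**The concern.** The exposure in the primary objective is what people eat. The exposure in the sample size is whether an animal is lean or obese. These are different quantities, and power for one says nothing about power for the other.

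The difference matters for interpretation. Suppose mucin-2 is lower in the obese group. That could reflect diet, but the two groups also differ in other ways. Type 2 diabetes is an exclusion for the lean controls but not for the obese group. The jejunal specimen is a surgical segment in one group and an endoscopic biopsy in the other. A group difference therefore does not isolate diet. If the objective is read as a question within obese patients, group does not vary at all and the comparison cannot address it. A reader who takes the 80% as the chance of detecting the diet association would be relying on a figure calculated for something else.

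**Working it through.** **Inputs from the protocol article.** Power section: means 1.00 and 0.65, with ± values 0.71 and 0.78 read as standard deviations; significance level 0.05; power 80%; 73 per group; 5% loss; 76 per group. Analysis section: "A 2-tailed *P* value <.05 will be considered statistically significant". Biopsies section: jejunal mucin-2 in the obese and endoscopy groups only.

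**Step 1: reproduce the stated sample size.**
- Difference: 1.00 − 0.65 = 0.35.
- Pooled SD: √[(0.71² + 0.78²)/2] = √[(0.5041 + 0.6084)/2] = √0.55625 = 0.746.
- Standardised difference: 0.35/0.746 = 0.469.
- Normal approximation: n = 2(1.960 + 0.842)² × 0.55625/0.35² = 2 × 7.849 × 0.55625/0.1225 = 71.3, so 72 per group.
- Exact noncentral t: 72.25, so 73 per group, with power 80.4%.
- A one-sided test would need 57, which does not match.

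The 73 is thus exactly the size for a two-sided two-sample comparison of means. The match also supports reading the ± values as SDs. No dietary quantity appears anywhere in the calculation.

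**Step 2: what the same numbers give for a diet–mucin-2 correlation.** By Fisher's z, the smallest correlation detectable with 80% power at two-sided 0.05 is r = tanh[(1.960 + 0.842)/√(n − 3)].
- Evaluable per group: 76 × 0.95 = 72.2, so 72.
- Obese group alone, n = 72: tanh(2.802/√69) = tanh(0.337) = 0.325, about 0.33.
- Obese plus endoscopy, n = 144: tanh(2.802/√141) = tanh(0.236) = 0.232, about 0.23.

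**Step 3: sensitivity to the unknown effect.** The document gives no expected diet–mucin-2 correlation, so the values of r below are assumptions shown as a range. The total needed is n = [(1.960 + 0.842)/atanh(r)]² + 3.

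| Assumed r | Participants needed for 80% power | Power with 73 obese patients |
|---|---|---|
| 0.20 | 194 | 40% |
| 0.25 | 124 | 57% |
| 0.30 | 85 | 74% |
| 0.35 | 62 | 86% |
| 0.40 | 47 | 94% |

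The power column uses the 73 before loss; 72 changes it little. Power for the stated objective could be well below or well above 80%, depending on a quantity that the plan does not give.

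**The case against.** The best defence is that this is a condensed journal article. Its list of tests is expressly open, and a regression or correlation model may well stand in a fuller plan that is not shown. That stands: the absence of a named regression is not in itself a fault. The tests are also introduced for comparisons among groups without saying which groups. A t test or analysis of variance could compare mucin-2 across categories of intake, and the abstract's wording of the objective would allow that. No such categories are defined, but the named tests do not rule them out.

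A reader might infer that the plan can never answer its primary question. The document does not support this: diet and mucin-2 are both measured in the obese and endoscopy participants, so the association can be estimated. A reader might also infer that the study is underpowered. That cannot be shown without an expected correlation.

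The phrase about obesity in the Introduction also has two readings: within obese patients, or obesity as a condition studied against lean controls. The figure of 0.33 belongs to the first reading.

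None of this reaches the sample size. The Power section is a complete, reproducible calculation for a contrast other than the one named in the objective. The article nowhere says that obese-versus-lean status stands in for diet.

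**Conclusion.** The point holds as a mismatch between the stated objective and the stated power. The 80% applies to a lean–obese mean difference of 0.469 SD taken from rats. It does not apply to the diet–mucin-2 association, and an obese–lean difference would not on its own establish that association.

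For the association, the planned numbers give 80% power only at an unadjusted correlation of about 0.33 (72 obese patients) or about 0.23 (144 with jejunal tissue). These figures assume the 5% loss, a simple correlation without covariates, two-sided 0.05, and the Fisher approximation. An adjusted model would change them somewhat. The conclusion goes no further than this: it does not say that the data are unfit for the question or that the true power is low.

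**What to change.** Choose one of two repairs and make the objectives, power and analysis sections agree.

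1. **Keep the diet objective.** Name one dietary exposure from the 7-day record; lipid intake follows from the stated hypothesis. Relate mucin-2 to it by regression or correlation within the obese group. If endoscopy participants are added, include a group term so that differences between the groups are not read as diet. State the power as the detectable unadjusted correlation: about 0.33 for 72, or about 0.23 for 144. Keep the 73-per-group calculation, labelled as the power for the separate obese–lean comparison.
2. **Keep the sample size as the primary justification.** Restate the primary objective as the obese–lean comparison of mucin-2, and make the diet association secondary.

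The choice of covariates and of scale for mucin-2 can be left to the investigators. Either repair is a change of wording and needs no new data or participants. The cost of the first is a less favourable power statement; the cost of the second is that diet is no longer the primary question. As the article reports recruitment still open, the choice should be recorded before the data are analysed.

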## Methods

### Study Design

This study will be conducted as a single-center prospective study, and it comprises a cross-sectional and a longitudinal part. In the cross-sectional part, differences at baseline between severely obese patients and lean subjects will be studied, focusing on the presence and severity of NAFLD, insulin resistance, T2DM and intestinal microbiota composition, Paneth cell products, and mucus composition. The longitudinal part will focus on changes in microbiota composition, Paneth cell products, and mucus in the severely obese group between baseline measurement and 1 year after RYGB.

### Ethical Approval and Recruitment

The Diet-Induced Alteration of Microbiota and Development of Obesity, Nonalcoholic Fatty Liver Disease, and Diabetes (DIAMOND) study is registered within the Netherlands National Trial Register (NTR560). The protocol was ethically approved by the official Independent Ethics Review Board of Máxima Medical Centre (reference 15.053) in November 2015. Written informed consent will be obtained from all participants. The study will be performed in accordance with the principles of the Declaration of Helsinki, as well as the guidelines of Good Clinical Practice. Recruitment started in the first quarter of 2016, and recruitment is currently ongoing. Patients deemed eligible for enrollment in either the obese group or the lean control (cholecystectomy) group are initially recruited by their surgeon or a specialized gastroenterology nurse at the time of approval for surgery or endoscopy. If interested in participation, the patient is contacted by the researcher and given detailed information about the study, in both oral and written form. After a 2-week period, the subjects are contacted to obtain informed consent, and then they will be officially enrolled in the study.

### Setting

Recruitment of patients and subsequent sampling are performed in a large teaching hospital in the Netherlands, which is awarded as a Center of Excellence in Metabolic and Bariatric Surgery.

### Study Population

The study population will comprise 3 groups: the obese group and 2 lean control groups. For the obese group, patients are screened by a multidisciplinary team, and they are approved for surgery according to the International Federation for the Surgery of Obesity and Metabolic Disorders guidelines. All patients with severe obesity and undergoing laparoscopic RYGB are considered eligible for inclusion. The surgical procedure is performed according to the circular stapling technique described by Dillemans et al [20].

Further inclusion criteria are a body mass index (BMI) between 35 and 45 kg/m^2^ and willingness to sign the informed consent form. Patients are excluded on the basis of the following criteria: (1) age<18 or >65, (2) presence of type 1 diabetes, substance abuse, inflammatory diseases, or neoplasms, (3) chronic use of corticosteroids prescribed by a physician, and (4) use of antibiotics in the 3 months preceding surgery.

For the 2 lean control groups, all patients with a BMI between 20 and 25 kg/m^2^ undergoing either upper gastrointestinal endoscopy or a laparoscopic cholecystectomy are eligible for inclusion. Patients are excluded on the basis of the following criteria: (1) age<18 or >65, (2) presence of type 1 or T2DM, substance abuse, inflammatory diseases, or neoplasms, (3) chronic use of corticosteroids prescribed by a physician, (4) use of antibiotics in the 3 months preceding surgery or endoscopy, and (5) presence of cachexia, defined as unintended weight loss (>5% in 1 month or >10% in 6 months). A flowchart for each of the groups is provided in Figure 1.

### Data Collection

#### Characteristics

Phenotyping of obesity will be based on measurement of body weight and calculation of BMI. Presence and severity of T2DM will be assessed by analysis of hemoglobin A1_c_ in blood, as well as analysis of plasma glucose and insulin levels, both fasting and during an oral glucose tolerance test. Presence of NAFLD will be determined on the basis of the liver biopsy, according to the validated Kleiner score [21]. Plasma levels of aspartate transaminase and alanine transaminase will be measured as markers of liver damage. Furthermore, plasma lipid spectrum, total leukocyte count, and differentiation count, as well as C-reactive protein, will be measured.

#### Dietary Habits

Dietary habits will be recorded using a Dutch food tracker [22], which can either be used as a Web-based program or as a smartphone app. All participants will be asked to record their diet for the duration of 7 consecutive days at baseline. The obese group will repeat this at 1-year follow-up.

#### Intestinal Microbiota Composition

Participants will be provided a stool sample collection kit and will be asked to sample their stool before surgery. The samples will be stored in the home freezer (–20°C) and transported to the hospital on the day of admission, where they will be stored in the laboratory freezer (–80°C) until analysis. Participants in the obese group will be asked to provide a second stool sample at 1-year follow-up. Stool samples will be analyzed according to the shotgun metagenomics approach. By sequencing the whole genome, we will be able to compare this with a reference genome and evaluate abundance of DNA fragments. This will include detecting the 2 primary intestinal phyla—Firmicutes and Bacteroidetes—as well as *Akkermansia muciniphila* abundance. Furthermore, we will analyze the fecal samples for presence of short-chain fatty acids, that is, acetate, propionate, and butyrate.

**Figure 1 figure1:**
[figure not shown]
Flow chart. DIAMOND: Diet-Induced Alteration of Microbiota and Development of Obesity, Nonalcoholic Fatty Liver Disease, and Diabetes; OGTT: Oral Glucose Tolerance Test.

#### Biopsies

In both the obese group and the lean control group, the following biopsies will be performed during laparoscopic surgery: visceral fat (omentum majus), liver, muscle tissue of the abdominal wall, and subcutaneous fat. In the obese group, a small segment of the jejunum will be collected during laparoscopic RYGB, a standard element of the procedure, and it will be used for analysis. In the control group, the jejunal full-thickness biopsy will be substituted by the endoscopically derived jejunal biopsy in the endoscopy group.

Directly after sampling, all tissues will be flash frozen and stored in the laboratory freezer (–80°C) until analysis. According to standard operating procedure protocol, the sampling in the obese group and lean cholecystectomy group will be performed by 3 surgeons involved in this study. The sampling in the lean endoscopy group will be performed by 1 gastroenterologist. The researcher will be present at the operating room and at the endoscopy suite at each procedure to flash freeze the samples directly after the biopsy. Stored data and materials will be only identifiable to the person by an assigned subject number. As such, patient privacy is guaranteed according to the Dutch Personal Data Protection Act.

The jejunal samples will be analyzed by means of quantitative PCR, specifically investigating HD5/DEFA5 lysozyme, mucin-1, and mucin-2, as well as Kruppel like factor 4 messenger RNA expression. Furthermore, a hematoxylin and eosin staining will be performed to allow for Paneth cell quantification. Liver samples will be taken to assess the presence and severity of NAFLD and nonalcoholic steatohepatitis, the use of the Kleiner score [21] will be done by a dedicated pathologist. Muscle tissue, visceral fat, and subcutaneous fat will be stored for future purposes to enable more detailed interorgan investigations of peripheral tissues involved in glucose and lipid homeostasis.

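### Jejunal mucin-2 is compared between surgical segments in all obese patients and endoscopic biopsies in all lean controls, so specimen type is fully aligned with group and no step to make the specimens comparable is described

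*Protocol article*

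**What the plan says.** The Biopsies section of the protocol article says that in the obese group "a small segment of the jejunum will be collected during laparoscopic RYGB". For lean controls: "In the control group, the jejunal full-thickness biopsy will be substituted by the endoscopically derived jejunal biopsy in the endoscopy group". The cholecystectomy controls give fat, liver and abdominal-wall muscle, but no jejunum. The Methods paragraph of the abstract makes the contrast explicit for the obese segment, "which will be compared with an endoscopically derived jejunal biopsy from the upper gastrointestinal endoscopy control group".

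On handling, the Biopsies section says: "Directly after sampling, all tissues will be flash frozen and stored in the laboratory freezer". On the assay: "The jejunal samples will be analyzed by means of quantitative PCR", with mucin-1, mucin-2, lysozyme, HD5/DEFA5 and KLF4 as targets. On operators, "the sampling in the obese group and lean cholecystectomy group will be performed by 3 surgeons involved in this study", and "The sampling in the lean endoscopy group will be performed by 1 gastroenterologist".

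The Power section names intestinal mucin-2 expression as the main outcome parameter and sizes the groups on a rat pilot: 1.00 (SD 0.71) in lean against 0.65 (SD 0.78) in obese animals.

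**The concern.** No lean participant has a surgical jejunal specimen and no obese participant has an endoscopic one. A difference in mucin-2 between the groups can therefore reflect obesity, specimen type or both, and adjusting for recorded covariates cannot tell them apart because there is no overlap.

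The mismatch also has a plausible direction. The Introduction describes "mucus components made by intestinal goblet cells" and antimicrobial proteins secreted by Paneth cells, so the main transcripts come from the epithelium. The Biopsies section itself presents the endoscopic biopsy as a replacement for a full-thickness one. A full-thickness sample also contains non-epithelial wall. If its RNA is extracted whole and expressed relative to a gene active in all layers, the epithelial signal is diluted in the obese group alone. That would lower apparent mucin-2 in obese patients, as the sample-size calculation assumes. A truly higher obese level could be masked in the same way. The Paneth-cell transcripts measured in the same samples share the problem.

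**Working it through.** **Step 1: who contributes which jejunal specimen**

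| Group | Jejunal specimen | Operator |
|---|---|---|
| Obese (RYGB) | surgical segment | 3 surgeons |
| Lean, cholecystectomy | none | – |
| Lean, endoscopy | endoscopic biopsy | 1 gastroenterologist |

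Specimen type and group coincide completely in the jejunal data.

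**Step 2: reproduce the planned sample size**

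Inputs from the Power section are means 1.00 and 0.65, SDs 0.71 and 0.78, alpha 0.05 and power 80%. The section on primary and secondary outcome analysis gives two-tailed testing.

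- Pooled SD = √((0.71² + 0.78²)/2) = √0.55625 = 0.746
- Standardised difference = 0.35/0.746 = 0.469
- Two-sample t-test (noncentral t): 73 per group, power 80.4%. This matches the stated 73. A one-sided test would need 57 and does not match.

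The trial is therefore sized on the lean-versus-obese contrast in mucin-2.

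**Step 3: illustrate the effect of dilution**

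Let f be the epithelial share of RNA in an obese sample relative to a lean one. The documents give no value for f, so it is an assumption shown over a range. With no true difference, the expected lean value is 1.00 and the expected obese value is f × 1.00, so the artefactual difference is 1 − f. The noncentrality of the t-test with 73 per group is (1 − f)/(0.746 × √(2/73)).

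| Assumed f | Artefactual difference | P(p<0.05), SD 0.746 in both groups | P(p<0.05), lean SD 0.71, obese SD 0.71 × f |
|---|---|---|---|
| 0.95 | 0.05 | 7% | 7% |
| 0.90 | 0.10 | 13% | 14% |
| 0.80 | 0.20 | 36% | 46% |
| 0.70 | 0.30 | 68% | 84% |

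The nominal figure is 5%. An f of 0.65 would reproduce the whole planned difference (1.00 − 0.65 = 0.35), and the chance then equals the planned power of 80%. That shows what dilution would be needed, not what is likely.

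**Step 4: if a true difference exists**

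With a true obese value of 0.65 and f = 0.80, the observed value would be 0.65 × 0.80 = 0.52. The difference would appear as 0.48 instead of 0.35.

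**Step 5: what is not touched**

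Associations between diet and mucin-2 within the obese group use one specimen type. The stool microbiota outcomes do not use jejunal tissue.

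**The case against.** The strongest reply is that the article is a condensed account. RNA extraction, the tissue layer used and the reference genes are not described for any sample. The Biopsies section mentions a standard operating procedure for sampling, so fuller working documents may exist, and one of them could provide for mucosal separation. That stands: the dilution is conditional on how the tissue is processed. The alignment of specimen type with group is not conditional, because the article states it.

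The size is also open. The share f is not in the documents. The model assumes proportional dilution and carries rat SDs over to human tissue. At f = 0.95 the error rate is close to nominal. This stands as well, and the figures are illustrations only.

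The researcher attends every procedure and freezes samples at once, which standardises handling after collection. It does not change what was collected. The article gives no mechanism by which the operator alone would alter mRNA, so operator is a residual difference and not the main point.

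Three stronger readings are tempting, and the documents do not support them:

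- *The bias favours the study's hypothesis.* The written hypothesis links dietary lipid intake to Paneth and goblet cell properties without a direction, and testing is two-tailed. Only the planning assumption has obese below lean.
- *No later analysis can help.* Normalising to an epithelial transcript addresses the tissue-composition part. Only differences in collection method and operator remain inseparable.
- *The main outcome is uninterpretable.* The Introduction states the primary objective as the relation of diet to mucin-2 in obesity, which can be studied within the obese group.

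Finally, endoscopic controls may be the only practical lean source of jejunum. The point accepts this and asks for no different biopsies.

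**Conclusion.** The concern holds in a limited form. As described, the obese-versus-lean comparison of jejunal mucin-2, on which the trial is sized, confounds specimen type with group. The limitations in the Discussion cover causality and the lack of repeat biopsies but not this mismatch.

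A downward bias in the obese group follows if whole-wall RNA is assayed against an ordinary reference gene and the endoscopic biopsy is richer in epithelium. Neither condition is stated in the article. The size cannot be derived from the documents: over an assumed f of 0.95 to 0.70, the chance of a false-positive result runs from 7% to 68%. A significant group difference could not be attributed to obesity without evidence that the specimens are comparable.

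**What to change.** 1. Extract RNA from the mucosal layer of the surgical segment where the frozen tissue allows. If a laboratory procedure already does this, state it.
2. Normalise mucin-2 and the Paneth-cell transcripts to an epithelial reference transcript in both groups.
3. Base the primary diet–mucin-2 inference on the analysis within the obese group. Treat the obese-versus-endoscopy contrast as exploratory unless the epithelium-normalised result agrees.
4. Add the specimen mismatch to the limitations in the Discussion.

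The cost is extra bench work, one more qPCR target and a more cautious claim for the group comparison. No new patients or biopsies are needed. Whether mucosa can be separated from tissue already frozen is for the laboratory to confirm. Differences in collection method and operator will remain and cannot be removed.
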